#### Interim analysis

One interim analysis will be performed when 50% of the participants completed the 30-day follow-up. The Z-statistic for the standardized treatment effect will be computed and compared with the O’Brien-Fleming type of boundaries for both efficacy and futility. Recruitment will stop if the Z statistic is larger than the efficacy boundary. The futility boundaries are non-binding and thus suggestive. The unblinded results of the interim analysis will be presented to an independent Data Safety and Monitoring Board (DSMB).

### Monitoring and safety

Independent Good Clinical Practice (GCP)-certified monitors from the UMC Utrecht will monitor the data collection and study progress. The frequency of these visits will be on a risk-based approach according to GCP guidelines.

Data entry will be verified using internal monitoring by a member of the coordinating study team. In addition, external monitoring will be performed by the independent monitors. During the monitoring visit, data entry will be verified on a random sample of the included patients by assessment of the source documents (e.g., electronic patient files, questionnaires or diaries). In the case of discrepancies or missing data, queries will be added to the questions that need revision or additional information.

#### Adverse events

Pre-OP consists of non-absorbable antibiotics. When taken orally, there is virtually no uptake of antibiotic components in the bloodstream. It is, therefore, expected that the occurrence of systemic side effects is negligible. More importantly, there is extensive experience with non-absorbable antibiotics applied as SDD on ICUs and severe and acute side effects that could apply to the current study have not been reported [27–30]. For this reason, we decided to refrain from an obligatory observation period after intake of the first dose of the study medication and patients can, therefore, take the medication at home. Nevertheless, patients will receive information about severe side effects of this study medication and are instructed to seek medical advice when they might suffer from severe acute side effects. The unblinding protocol can be freely assessed via our website, when deemed necessary. Late side effects, such as the development of antibiotic resistance, have not been described either [31–35]. Nevertheless, the occurrence of side effects and the development of antibiotic resistance will be monitored as secondary endpoints of this study.

All adverse events will be reported to the principle investigator. Serious adverse events (SAEs), serious adverse reactions (SARs) and suspected unexpected serious adverse reactions (SUSARs) will be reported to the sponsor within 24 h after notification of the event. For the SAEs, we decided to only report life-threatening infections with colistin- or tobramycin-resistant bacteria or *C. difficile* colitis within 24 h. Postoperative complications that are known to occur after colorectal surgery and are not directly related to the study medication will be reported to the ethical board in periodic line-listings and not within the 24-h time window.

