#### Evaluable patients

Patients who start with the 3-day intervention period but for whom surgery is cancelled or postponed for more than 7 days, will not be evaluable for analysis of the primary and secondary outcomes. Sample size calculations are based on evaluable patients and, herewith, assumes replacement of all non-evaluable patients. A limit of 7 days is chosen as a cut-off to ensure that patients are not re-colonized at the time of surgery, since it is expected that the effects of decontamination will last for a least several days when the 3-day treatment course is completed.

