### Outcome measures

As a primary composite endpoint, we will investigate the efficacy of Pre-OP on deep SSI and/or mortality within 30 days after surgery. The secondary endpoints including their definitions are summarized in Table 2.

**Table 2 Tab2:** Definition of endpoints

Endpoints	Definitions
Primary composite endpoint	
Cumulative incidence of deep surgical site infection and/or mortality within 30 days after surgery	Deep SSI will be diagnosed according to the CDC criteria for surgical site infections [37]. Deep SSI includes both deep incisional SSI and organ/space SSI
Secondary endpoints	
*30 days after surgery*	
Cumulative incidence of superficial SSI	Superficial and deep SSIs will diagnosed according to the CDC criteria for surgical site infections [37]
Cumulative incidence of deep SSI	
All-cause mortality	
Cumulative incidence of bacteremia	Blood cultures positive for microorganisms
Cumulative incidence of infection with *Clostridium difficile*	Stool sample positive for *C. difficile* toxins
Cumulative incidence of infection with HRE	Clinical cultures positive for ESBL or carbapenemase-producing *Enterobacteriaceae* or *Enterobacteriaceae* resistant to quinolones and/or aminoglycosides [38]
Cumulative incidence of rectal colonization with HRE and colistin resistant species	Rectal swabs positive for HRE or colistin resistant species, measured at baseline and 30 days after surgery
Cumulative incidence of anastomotic leakage	Clinical and/or radiological evidence of leakage requiring surgical or radiological reintervention
Cumulative incidence of re-laparotomy	Reoperation in the abdominal region
In-hospital use of antibiotics	Defined as “days on therapy”
*6 months after surgery*	
All-cause mortality	
Quality of life	Measured with the RAND-36 questionnaire [39]
Length of hospital stay	In days, including all readmissions
Length of ICU stay	In days, including all readmissions
In-hospital costs	

*CDC* Centers for Disease Control and Prevention, *ESBL* extended-spectrum beta-lactamase, *HRE* highly resistant *Enterobacteriaceae*, *ICU* intensive care unit, *SSI* surgical site infection

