### Assessment and follow-up

#### Study procedures

The study procedures are listed in Table 3. The preoperative study procedures will take place during visits to the outpatient clinic. These visits will be routinely scheduled and will not be planned as study-specific procedures. During the first visit, the trial will be explained and patients will receive an information letter. Informed consent will be signed during a second preoperative visit. During this visit, the study medication will be provided along with instructions for use and a study diary. Furthermore, the first rectal swab will be taken and patients will receive the first quality-of-life questionnaire. The study diary will be used to document the intake of study medication and to report potential side effects due to the study medication. Patients will take the study medication according to the instructions during the 3 days prior to surgery. The bottles with remainders of study medication will be collected at hospital admission and will be weighted to estimate treatment adherence. The study diaries will also be collected at admission.

**Table 3 Tab3:** Study flow

	Study period							
	Screening^b^	Enrollment^b^	Intervention			Follow-up and postoperative procedures^c^		
			day					
Time point^a^	~ − 2 weeks	~ − 2 weeks to day − 4	−3	−2	−1	Day 0	Day 30	Month 6
Patient recruitment	X							
Eligibility screening		X						
Informed consent		X						
Allocation		X						
Rectal swab		X					X	
Intake study medication			X	X	X			
Surgery						X		
Estimation of compliance			X	X	X			
Patient characteristics	X	X						
Surgical characteristics						X		
Primary endpoint Deep SSI and/or mortality							X	
Secondary endpoints								
Superficial SSI							X	
Anastomotic leakage							X	
Re-laparotomy							X	
Bacteremia							X	
Rectal colonization with HRE or colistin resistant species							X	
Infection with HRE							X	
Infection with *Clostridium difficile*							X	
In-hospital antibiotic use							X	
Length of hospital stay								X
Length of ICU stay								X
All-cause mortality							X	X
In-hospital costs								X
Quality of life		X						X
Adverse events		X	X	X	X	X	X	X
Serious adverse events		X	X	X	X	X	X	X
SUSARs/SARs			X	X	X	X		

*HRE* highly resistant *Enterobacteriaceae*, *ICU* intensive care unit, *SAR* serious adverse reaction*, SSI* surgical site infection, *SUSAR* serious unexpected adverse reaction

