### Statistical analysis

The primary composite endpoint will be analyzed according to the intention-to-treat principle. All patients who were randomized to receive study medication and who underwent colorectal surgery will be included in this analysis. The difference in the primary outcome between Pre-OP and placebo will be estimated with a Z-test for proportions or by logistic regression, correcting for the stratification variable (study site). Multivariable logistic regression will be used and measured confounders will be fitted in the model as covariates. Secondary outcomes will be analyzed using the chi-square test, Fisher’s exact test, logistic regression, time-to-event analysis, *t* test or Mann–Whitney *U* test, when appropriate. Missing data will be analyzed and handled using.

Exploratory subgroup analyses will be performed for study center, age, sex, Body Mass Index (BMI), ASA classification, preoperative use of immunosuppressive drugs, preoperative radiation of the surgical site, indication for surgery, wound class, surgical procedure, duration of surgery and timing of perioperative intravenously administered antibiotic prophylaxis. Per-protocol analyses will be performed in addition to all the intention-to-treat analyses.

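### Side effects are called a secondary endpoint, but Table 2 does not list them, and patients who took study drug without timely surgery are excluded from all secondary outcomes

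*Protocol article*

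**What the plan says.** Three parts of the protocol article bear on this point.

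- **Adverse events:** it states: "Nevertheless, the occurrence of side effects and the development of antibiotic resistance will be monitored as secondary endpoints of this study".
- **Outcome measures:** the text refers the reader to Table 2 for the secondary endpoints and their definitions. Table 2 has *C. difficile* infection, infection with highly resistant Enterobacteriaceae, and rectal colonization with resistant species, all under the heading for 30 days after surgery. It has no row for side effects or adverse events.
- **Evaluable patients:** the rule covers "Patients who start with the 3-day intervention period but for whom surgery is cancelled or postponed for more than 7 days". These patients "will not be evaluable for analysis of the primary and secondary outcomes", and the sample size "assumes replacement of all non-evaluable patients". The 7-day limit is justified by the wish to avoid re-colonization at the time of surgery.

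On data collection, the Study procedures section says: "The study diary will be used to document the intake of study medication and to report potential side effects due to the study medication". Diaries are handed in at hospital admission. Table 3 schedules adverse events and serious adverse events from enrollment to month 6.

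**The concern.** Read together, the three parts do not fit. Side effects are declared a secondary endpoint, the list of secondary endpoints leaves them out, and a general rule removes some exposed patients from every secondary outcome.

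The reason given for that rule concerns efficacy. A patient whose gut flora has returned before surgery no longer tests the prophylaxis. This says nothing about a side effect on days -3 to -1, which has already happened whether or not surgery follows.

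At stake is the randomized comparison of side effects. Study drug is taken before surgery, so being operated on in time is a post-randomization event. Conditioning a harm comparison on it is harmless only if cancellation or postponement is unrelated to harm. The plan does not say so and cannot guarantee it.

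**Working it through.** **Consistency of the text**

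| Question | Where | Answer in the plan |
|---|---|---|
| Are side effects a secondary endpoint? | Adverse events | Yes |
| Is a side-effect endpoint defined? | Table 2 | No |
| Are resistance endpoints defined? | Table 2 | Yes, at 30 days after surgery |
| Are exposed patients without timely surgery in the secondary analyses? | Evaluable patients | No, and no safety exception |
| Are their adverse events recorded? | Table 3; Adverse events | Yes, no limit to evaluable patients |
| Does the DSMB see their serious events? | Data Safety and Monitoring Board | Yes, no limit to evaluable patients |
| Is their diary collected? | Study procedures | Only at admission; no collection point is stated if surgery is cancelled before admission |

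The Statistical analysis section names no separate population for harms. Its one stated set, for the primary analysis, also requires surgery: "All patients who were randomized to receive study medication and who underwent colorectal surgery will be included in this analysis".

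**How many patients could be outside the comparison**

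The plan gives no figure for this. The 966 evaluable patients in the Sample size section serve only as an input and are not disputed here. A standard pooled two-proportion calculation (14% versus 8.4%, one-sided 2.5%, 80% power) gives 497 per arm, 994 in total. That is 2.9% above 966, and 483 per arm has 78.9% power.

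Let *s* be the share of patients starting drug who become non-evaluable. With full replacement up to 966 evaluable, the number excluded is 966 × *s* / (1 − *s*). The values of *s* are assumptions.

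- *s* = 3%: 966 × 0.03 / 0.97 = 29.9, about 30
- *s* = 5%: 966 × 0.05 / 0.95 = 50.8, about 51
- *s* = 10%: 966 × 0.10 / 0.90 = 107.3, about 107

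These counts cover both arms and every reason for cancellation.

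**What share of side-effect events would be missed**

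Assume a side-effect rate of 5% in evaluable patients and a rate *r* in excluded patients. The share missed is *s r* / [(1 − *s*) × 0.05 + *s r*].

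| *s* | *r* = 5% (cancellation unrelated to harm) | *r* = 30% (related) |
|---|---|---|
| 3% | 3% | 0.009 / 0.0575 = 16% |
| 5% | 5% | 0.015 / 0.0625 = 24% |
| 10% | 10% | 0.030 / 0.0750 = 40% |

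In the unrelated case the loss is proportional and the rate among analysed patients stays at 5%. Only in the related case does the analysed rate understate the rate among all exposed patients (for *s* = 5%, 5.0% against 6.25%). Both rates are illustrative; neither comes from the documents.

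**The case against.** The strongest reply is that harm recording does not depend on evaluability. Adverse events are scheduled from enrollment through the dosing days to month 6, all are to be reported to the investigator, and the DSMB acts on lists of serious events that are not restricted to operated patients. A severe reaction on days -3 to -1 would be captured. One may add that, if side effects are not in Table 2, the evaluability rule need not reach them, and that a journal article commonly leaves the safety population to the full protocol or the SAP.

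Much of this stands. Harms are recorded. Resistance is properly listed in Table 2. A patient who is never operated on has no outcome at 30 days after surgery by definition.

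It does not remove the conflict. Recording and listing events is not the endpoint comparison that the Adverse events section announces. The DSMB lists cover serious events, so mild effects reported only in the diary are not on them. Nor is this merely a missing detail: the article states an exclusion from all secondary outcomes and states that side effects are one of them. An analysis plan that followed the article would inherit the exclusion.

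A reader might go further and infer that drug harm is under-counted, or that the comparison is tilted in favour of the active arm. The documents do not support this. They give no cancellation rate, do not say that harm leads to postponement beyond 7 days, and do not suggest that this would be commoner in one arm. The Adverse events section in fact expects systemic side effects to be negligible.

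**Conclusion.** The point holds as an inconsistency that should be corrected. Side effects are named as a secondary endpoint, are not defined as one, and would be compared without some of the patients who took study drug. The recording of harms is not affected, and neither the primary analysis nor the sample size is in question here.

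The size depends on an unknown cancellation rate: about 30 to 107 exposed patients over both arms if 3% to 10% become non-evaluable. Bias between the arms is a possibility that needs harm-related cancellation or postponement. It is not something that the documents show.

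**What to change.** Reconcile the Evaluable patients section, Table 2 and the Adverse events section:

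- Limit the evaluability exclusion to the efficacy outcomes counted from surgery.
- Add side effects and adverse events by arm to Table 2.
- Analyse them in all randomized patients who took at least one dose, operated on or not. Use the adverse event data already scheduled from enrollment, and the diary where it can be retrieved.
- For the resistance outcomes, which are timed from surgery, say whether patients who were not operated on contribute at all.

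The cost is a change of wording, one extra analysis set, and the effort of retrieving diaries from patients who were not operated on. No further patients are needed.

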#### Data Safety and Monitoring Board

A Data Safety and Monitoring Board (DSMB) is established to guard patient safety during the trial. The DSMB consists of four independent experts who will have an active role during the entire study period. The board will issue recommendations to continue or stop the study, based on the unblinded results of the interim analysis and on the list of SAEs, SARs and SUSARs.

## Discussion

Undergoing surgery is associated with an increased risk of surgical site infections, but also mortality. To overcome the issue of mortality being a competing risk with the development of deep SSIs, our primary outcome of interest, we decided to use a composite endpoint for our primary outcome. Thirty-day all-cause mortality and deep SSIs will also be analyzed separately as secondary endpoints.

The rationale behind our intervention is to decontaminate the digestive tract prior to surgery, where we hypothesize that by lowering the bacterial load in the colon and rectum during the surgical procedure, the risk of postoperative infections is reduced. In a previous study, a suspension of colistin sulphate, tobramycin and amphotericin B was used to reduce anastomotic leakage and postoperative infectious complications [24]. This suspension is identical to the suspension that is used as an antibiotic prophylaxis on Dutch ICUs, often referred to as SDD). In contrast with SDD, the solution that will be used in our study does not contain an antifungal component (amphotericin B or nystatin). Fungi are rarely identified as the causative pathogens of SSIs after surgical procedures on the lower gastrointestinal tract and it was, therefore, decided to omit the antifungal component [36]. Another difference between our study and the trial by Roos et al. is the timing of the treatment. In the previous trial, the intervention started 2 days prior to surgery and was continued during the postoperative period until normal bowel movements were observed. In our study, the intervention will only be given preoperatively and is discontinued on the night before the surgical procedure. We hypothesize that the majority of SSIs is caused by intraoperative rather than postoperative contamination of the surgical site and that the greatest reduction in SSIs will, therefore, be achieved by ensuring that the colonic bacterial load is at its lowermost at the time the surgical procedure takes place. The prophylaxis in our study is, therefore, restricted to the preoperative period. We also hypothesize that the treatment period of 3 days will be sufficient since we expect that the decontamination will least for several days. In our opinion, continuation of the prophylaxis in the postoperative period is not necessary as this could adversely increase the risk of developing antibiotic resistance or opportunistic infections.

To date, there is no consensus on the use of preoperative orally administered antibiotic prophylaxis prior to colorectal surgery in addition to perioperative intravenously administered antibiotic prophylaxis and without concurrent use of MBP. This impedes the formulation of clear-cut recommendations on its use in current infection control guidelines. This randomized, placebo-controlled, double-blind multicenter study aims to determine the efficacy of Pre-OP in addition to perioperative intravenously administered antimicrobial prophylaxis on the development of SSIs and other infectious and non-infectious complications. The proposed study design offers an optimal approach to adequately minimize bias and generate generalizable results in order to guide important evidence-based recommendations regarding infection control measures in colorectal surgery (Additional file 2).

### Trial status

The trial received ethical approval in September 2016. The recruitment of patients started in April 2017.

## Abbreviations

CPE: Carbapenemase-producing *Enterobacteriaceae*
DSMB: Data Safety and Monitoring Board
eCRF: Electronic Case Report Form
ESBL: Extended-spectrum beta-lactamase
GCP: Good Clinical Practice
HRE: Highly resistant *Enterobacteriaceae*
ICU: Intensive care unit
MBP: Mechanical bowel preparation
Pre-OP: Preoperative orally administered antibiotic prophylaxis
SAE: Serious adverse event
SAR: Serious adverse reaction
SDD: Selective decontamination of the digestive tract
SSI: Surgical site infection
SUSAR: Suspected unexpected serious adverse reaction
